# Impact of Intranasal Administration of Ayurveda Medicine in Apparently Healthy Individuals on Neurophysiological Variables and Functional Connectivity Using Functional Magnetic Resonance Imaging: Protocol for an Exploratory Randomized Controlled Trial

**DOI:** 10.2196/67132

**Published:** 2026-01-09

**Keywords:** nasya, healthy individuals, neurophysiology, functional magnetic resonance imaging, functional MRI, blood oxygen level–dependent, BOLD, intranasal

## Abstract

**Background:**

*Nasya**karma*, an Ayurveda nasal drug delivery system, is considered a potent therapeutic modality in *panchakarma* treatment. Uniquely, nasal drug delivery can bypass liver metabolism and the blood-brain barrier for faster drug delivery. Available studies on *nasya karma* focus mainly on its efficacy. This pioneering study aims to explore the mechanisms of *nasya karma* on brain function and neurophysiology, investigating its potential to modulate activity in specific brain regions and affect the functional connectivity between these regions using functional magnetic resonance imaging (fMRI).

**Objective:**

The study aims to map the neurophysiological response of the brain to *nasya karma* using blood oxygen level–dependent fMRI in both rest and task phases and assess the impact of *nasya karma* on quality of life, cognition, sleep, and psychological well-being in healthy volunteers.

**Methods:**

A total of 60 healthy volunteers in the age group of 20 to 40 years who fulfill the selection criteria will be recruited for this randomized controlled trial at the National Ayurveda Institute for Panchakarma, Cheruthuruthy, Kerala, India, and randomized in a 1:1 ratio to either the intervention group (n=30; group 1, receiving *nasya karma* with *anu taila*, an oil-based formulation manufactured using a paste and decoction of herbal medicines with oils as the base material, for a period of 14 days) or the control group (n=30; group 2, not receiving any intervention). The participants will undergo task-based and resting fMRI on day 1 (twice on day 1 before administration and 15 minutes after *nasya karma* for participants in group 1) and day 14 to map the neurophysiological response to *nasya karma* of the brain. A comprehensive neuroimaging protocol using structural magnetic resonance imaging and fMRI will be used in the study. The effect of *nasya karma* on sleep, psychological well-being, cognition, and quality of life will be assessed on the 1st and 30th days in both groups.

**Results:**

After the data collection process of this randomized controlled trial is completed, the study will go into the analysis stage, in which the collected data will be subjected to robust statistical analysis. The final results of the study are expected to be published in 2026.

**Conclusions:**

This study will investigate the neurophysiological mechanisms of *nasya karma* by examining clinical, neuropsychological, and neuroimaging variables to identify associated neural patterns to develop therapeutic protocols for many diseases. The findings will also provide evidence for future research supporting the use of *nasya karma* as a practical and noninvasive therapeutic modality for treating cerebrovascular, behavioral, and neurological disorders as indicated in Ayurveda. The study will propel innovative research focusing on the neural mechanisms responsible for the delivery of central nervous system therapeutics to the brain, thereby bypassing the blood-brain barrier and yielding favorable outcomes in central nervous system diseases.

**Trial Registration:**

Clinical Trials Registry – India CTRI/2023/06/054219; hhttps://ctri.nic.in/Clinicaltrials/pmaindet2.php?EncHid=ODQ1OTU=&Enc=&userName=

**International Registered Report Identifier (IRRID):**

DERR1-10.2196/67132

## Introduction

### Background

In Ayurveda, *nasya karma* is among the *panchakarma* procedures, a set of 5 therapeutic modalities for body purification involving nasal administration of medicine, and is regarded as a potent approach in health promotive, preventive, and therapeutic applications. The therapeutic applications of *nasya karma* span a wide clinical spectrum, addressing conditions such as chronic sinusitis, cervical spondylosis, and various neurological and psychiatric disorders. *Nasya*
*karma* is the only procedure that uses the nasal route for medicine administration to deliver therapeutic agents directly to the central nervous system (CNS), bypassing the digestive tract and potentially enhancing the efficacy of treatment owing to its faster absorption.

Intranasal drug administration has gained considerable traction for many decades as a noninvasive route for delivering medications targeting local, systemic, and CNS effects. The leaky intercellular junctions of the nasal mucosa and the extensive vascularity of the lamina propria and nasal mucosa facilitate optimal drug absorption, positioning intranasal delivery as a highly effective and versatile method for a wide range of therapeutic applications [1,2]. In the context of neurological disorders, intranasal drug delivery is advantageous due to its ability to achieve high drug levels in the brain, providing a direct pathway that bypasses the blood-brain barrier (BBB) more effectively than traditional parenteral and oral routes, especially considering that the anatomical features allow for rapid drug absorption, a noninvasive administration method, and the avoidance of hepatic first-pass metabolism, leading to faster therapeutic effects [3]. Direct absorption of molecules through the trigeminal and olfactory pathways provides a direct route to the brain, resulting in a favorable pharmacokinetic and pharmacodynamic profile by bypassing major physiological barriers such as the BBB and the blood–cerebrospinal fluid barrier [4].

The unique relationship that exists between nasal cavity and cranial cavity tissues makes intranasal drug delivery to the brain more feasible and effective. Intranasal delivery provides drugs with short channels to bypass the BBB, greatly enhancing the therapeutic effect on the neurological disease spectrum [5].

*Panchakarma* encompasses a comprehensive set of Ayurvedic detoxification procedures, including *vamana* (emesis), *virechana* (purgation), *nasya* (nasal administration of herbal oils or powders), *basti* or *vasti* (herbal enema), and *raktamokshana* (bloodletting) [6]. *Panchakarma* is a mainstay of Ayurveda clinical practice where the physician can choose any of the 5 sets of therapeutic modalities to bring about a homeostatic equilibrium in the body tailored to each individual depending on the intended purpose of use (promotive, preventive, therapeutic, or rehabilitative), body constitution, *dosha* (the body humors or functional principles that govern physiological and psychological processes), health or disease status, age, and fitness to undergo the *panchakarma* procedure.

*Anu taila* [7] is an oil-based formulation manufactured using a paste and decoction of herbal medicines with oils as the base material. The ingredients are combined in specific proportions as highlighted in classic Ayurvedic texts and subjected to a unique heating process to meet certain pharmaceutical parameters, ensuring the retention of both water-soluble and lipid-soluble principles at optimal levels. *Anu taila* can be likened to liposomes, where nanoparticles comprise lipid bilayer membranes surrounding an aqueous interior. The higher viscosity of this formulation increases contact time between the drug and the nasal mucosa, thereby enhancing permeation, and the viscosity may influence mucociliary clearance, potentially reducing it and, thus, prolonging the formulation’s retention time in the nasal cavity, which can lead to increased drug absorption [8,9].

Despite its extensive use as a therapeutic modality in clinical practice across a wide range of conditions and in healthy individuals to maintain health and homeostasis, the exact mechanism of action of *nasya karma* remains obscure and mysterious, primarily due to a lack of physiological or mechanistic studies in this area. Given the paucity of research on the neurophysiological mechanisms underlying *nasya*, this study aims to use functional magnetic resonance imaging (fMRI) to investigate its potential to modulate activity in specific brain regions and affect the functional connectivity between these regions. Understanding these neurophysiological correlates is crucial as it will elucidate whether *nasya karma* exerts targeted effects or has more widespread, nonspecific impacts on the brain’s intrinsic functioning. This knowledge will benefit stakeholders by providing a scientific basis for conceptualizing future research, potentially leading to optimized therapeutic protocols, improved clinical outcomes, and enhanced integration of *nasya karma* into modern medical practice. By establishing clear spatial and temporal patterns of brain activity associated with *nasya karma*, this study could pave the way for more precise and effective applications of this traditional Ayurvedic practice in contemporary health care. This may also propel innovative research focusing on the neural mechanisms responsible for the delivery of CNS therapeutics to the brain, thereby bypassing the BBB and yielding favorable outcomes in CNS diseases.

Although *nasya karma* is extensively used for neurological and systemic health benefits, no studies have elucidated its neurophysiological mechanisms of action, specific brain region targets, or the connectivity changes underlying its effects. This knowledge gap prevents scientific validation and optimized therapeutic application of *nasya karma* in clinical neuroscience. This study addresses this gap by using fMRI to characterize the brain’s response to *nasya karma*, thereby providing mechanistic insights essential for evidence-based integration of this ancient intervention into modern CNS therapeutics.

### Objectives

The primary objective of this study is to investigate the neurophysiological activity of the brain induced by the *nasya karma* procedure using blood oxygen level-dependent (BOLD) fMRI to elucidate the comprehensive neural response to *nasya karma* both in the rest and task phases. The secondary objective is to examine the impact of the *marsha nasya karma* (Ayurveda nasal drug delivery using a medicated or nonmedicated lipid medium) procedure on health parameters in apparently healthy volunteers, such as quality of life; cognition; sleep; and psychological well-being through anxiety, stress, and cognitive health.

The research hypothesis for this study is that the administration of *marsha nasya karma* with *anu taila* will increase the activation of different brain areas and enhance functional connectivity in different neuronal networks compared to baseline.

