### Interventions

The participants in the intervention group will be administered *nasya karma* (nasal instillation) with *anu taila* at a dose of 3 mL per nostril for 7 days (on every alternate day for 14 days) as indicated in the Ayurveda treatises for healthy individuals. Before *nasya*, local oleation and sudation of the head region will be conducted for approximately 10 minutes. Following the *nasya karma* procedure, participants will inhale medicated smoke and rinse their mouths with lukewarm water. The control group, consisting also of healthy individuals, will not undergo any interventions to facilitate assessment of the specific effects attributed to *nasya karma* in the intervention group when compared to baseline measures in healthy individuals.

*Nasya karma* will be administered by the investigator at the hospital’s *panchakarma* unit except on assessment days, when it will be conducted at AIMS. Each participant will be closely monitored for 30 minutes following the procedure to observe any immediate effects or reactions. Vital signs such as heart rate, blood pressure, and respiratory rate will be monitored and recorded before and after every session. Participants reporting any adverse symptoms experienced after each session will be recorded through a standardized format designed to capture a wide range of potential side effects, including nasal irritation, headache, dizziness, nausea, or any other discomfort. Any serious adverse event will be reported immediately to the institutional ethics committee, and a causality assessment will also be conducted. Appropriate care will be provided for all adverse events requiring medical intervention, and they will be followed up on until resolution or stabilization.

If a participant experiences significant adverse effects, such as severe nasal irritation, fever, sinusitis, or any other serious discomfort that impacts their well-being, the intervention will be immediately halted, and the participant will be withdrawn. Discontinuation will also occur in cases of noncompliance with the treatment regimen, if the participant wishes to withdraw for any reason, or if the participant meets any of the exclusion criteria during the study. As the trial involves healthy volunteers, administration of concomitant medication is prohibited during the trial period of 30 days.

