This study is structured as an exploratory randomized controlled clinical trial, with participants allocated in a 1:1 ratio to the intervention and control groups, matched for age and sex to comprehensively assess and evaluate the neurophysiological and holistic health effects of the *marsha nasya karma* procedure in comparison to a control group (Figure 1). Settings of the study include NARIP and AIMS.

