### Detailed Methodology of the Primary Outcome Measure

#### Overview

The primary outcome measure encompasses 2 key components. The first is the assessment of the immediate neurophysiological response elicited by *nasya karma* during both the resting and task phases using MRI. The second component is the evaluation of the neurophysiological response elicited by *nasya karma* after 14 days (following 7 days of nasya) during both the resting and task phases using MRI. Functional neuroimages will be collected using a 3-Tesla scanner (Discovery MR750w; GE HealthCare). Resting state fMRI data will include 3D T1-weighted structural imaging with a fast-spin echo sequence and BOLD imaging with a spin echo, gradient echo, and echo-planar imaging sequence for 40 minutes, covering the entire brain. The parameters for 3D-T1 imaging will include a slice thickness of 1 mm; a repetition time and echo time of 8.5 milliseconds and 3.2 milliseconds, respectively; a field of view of 256 × 256 × 142 mm^3^; a flip angle of 12°; a matrix of 256 × 256; an in-plane resolution of 1 × 1 × 1 mm^3^; and 142 layers. The parameters for BOLD imaging will include a slice thickness of 3.2 mm; a repetition time and echo time of 3000 milliseconds and 30 milliseconds, respectively; a flip angle of 80°; a matrix of 64 × 64; a field of view of 256 × 256 × 142 mm^3^; 35 layers; and 150 time points.

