#### Statistical Analysis

##### Overview

The modified intention-to-treat principle will guide the analysis for all outcomes within the full analysis set. Quantitative data will be summarized using mean, SD, minimum, maximum, and median values. Enumeration data will be presented as frequency and the corresponding percentage. Intragroup comparisons will be conducted using the Student paired *t* test or Wilcoxon signed rank test for continuous variables and the chi-square test for categorical variables. Intergroup comparisons will be conducted using the independent-sample *t* test or the Mann-Whitney *U* test. Significance thresholds will be set at *P*<.05 for all 2-tailed tests.

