##### fMRI Data Analysis

The fMRI data will undergo preprocessing using either the Data Processing and Analysis for Brain Imaging or CONN toolboxes, which will encompass essential steps such as slice timing correction, realignment for motion correction, regression to remove confounding effects, normalization to a standard template, smoothing to enhance signal-to-noise ratio, detrending to remove low-frequency drifts, and filtering to focus on relevant frequency bands, aligning with established practices in the field. After data preprocessing, amplitude of low-frequency fluctuation, functional connectivity, and large-scale functional brain network analysis will be conducted to investigate the difference in neurophysiological responses between the groups. The results will be interpreted in the context of the experimental paradigm to elucidate neural correlates of the studied phenomena, providing insights into the effects of *nasya karma* on brain function. Voxels exhibiting expected time-course correlations (30-second periods) will receive high activation scores, whereas those showing no correlation or deactivation will receive lower or negative scores, respectively. MRI data analysis will use general linear models via statistical parametric mapping (SPM). fMRI data will be processed using MATLAB 2023 (MathWorks Inc).

Resting phase MRI data will be analyzed using software tools such as SPM, the CONN toolbox, and the Functional Magnetic Resonance Imaging of the Brain Software Library (Analysis Group), whereas task phase fMRI will specifically use SPM. Given the focus on group data in this study, complex patterns of brain activation will be interpreted collectively rather than individually. For voxel-based analysis, a significance threshold of *P*<.01 at the voxel level and *P*<.05 corrected for false discovery rate (FDR) at the cluster level will be applied. Connectome-based analysis will use a threshold of *P*<.05 corrected for FDR. Additionally, Pearson correlation analysis will be performed to explore potential associations between clinical outcomes and fMRI findings, examining changes in brain activity following different interventions.

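### The only research hypothesis is worded as a rise from baseline, which conflicts with the randomized between-group comparison that the design and the fMRI analysis describe

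*Protocol article*

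**What the plan says.** All references are to the protocol article.

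- **Objectives.** The single research hypothesis is that the procedure "will increase the activation of different brain areas and enhance functional connectivity in different neuronal networks compared to baseline". The control group is not mentioned.
- **Interventions, on the control arm.** Controls receive nothing, so that specific effects of nasya can be assessed "when compared to baseline measures in healthy individuals". This wording is mixed: the control arm is there to isolate an effect, yet the reference named is baseline.
- **Interventions, design paragraph.** Allocation is 1:1 and effects are to be evaluated "in comparison to a control group".
- **Statistical Analysis, Overview.** "Intragroup comparisons will be conducted using the Student paired" t test or the Wilcoxon signed rank test; "Intergroup comparisons will be conducted using the independent-sample" t test or the Mann-Whitney test. Both use two-tailed .05, and neither is called primary or supportive.
- **fMRI Data Analysis.** Amplitude, connectivity and network analyses are run "to investigate the difference in neurophysiological responses between the groups".
- **Detailed Methodology of the Primary Outcome Measure, Overview.** "The primary outcome measure encompasses 2 key components": the immediate response and the response after 14 days, each at rest and on task.
- **Abstract (Methods) and Table 1.** The nasya group is scanned twice on day 1 and once on day 14. Controls are scanned once on each of those days.

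**The concern.** A hypothesis tells the reader which result would support it. Here it points to a contrast that makes no use of the randomization. A change from baseline within one arm combines any effect of nasya with whatever else happens between scans, such as task practice, familiarity with the scanner or the passage of time. The control group is there to remove those influences, and it does so only if the hypothesis refers to it.

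The same data could therefore satisfy the hypothesis as written and show no difference between the randomized groups. Both kinds of test are planned at the same level with no ranking, so the article gives no rule for reading such a split result.

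**Working it through.** **1. The sections side by side.** The hypothesis gives baseline as the comparator. The design paragraph and the fMRI analysis section give the control group. The sentence on the role of the control arm mentions both ideas. The statistical overview lists both kinds of test. No section reconciles them.

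**2. What each primary component can support.** Controls have scans on days 1 and 14, so the day-14 component can be a between-group difference in change. They have only one day-1 scan, so the immediate component has no control counterpart and can only be a within-arm change.

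**3. The plan's own figure.** Power Analysis gives more than 80% power for d=0.6 with 30 per group, at voxel P<.001 and cluster-level FWE P<.05. It does not say whether d is within or between groups. With noncentral-t power, two-sided:

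- Between groups: noncentrality = d × √(n/2) = 0.6 × √15 = 2.32 on 58 df. Power is 62.8% at .05 and 14.2% at .001.
- Within one arm (paired): noncentrality = d × √n = 0.6 × √30 = 3.29 on 29 df. Power is 88.8% at .05 and 38.0% at .001.

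Of these four, only the paired test at .05 exceeds 80%. The toolbox's cluster-level power cannot be rebuilt from the inputs given. So the power statement does not settle which contrast is meant.

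**4. How far the two contrasts can part.** Inputs: 30 per arm (Sample Size), two-sided .05 (Statistical Analysis, Overview) and voxel .001 (Multiple-Comparison Correction). Assumptions: no nasya effect, one normally distributed measure, and the same mean change δ in both arms, in SDs of the change score. The article gives no value for δ, so a range is shown. The within-arm test has noncentrality δ × √30 on 29 df. The critical values are 2.045 at .05 and 3.659 at .001.

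| Shared drift δ | Noncentrality | Significant rise in nasya arm, .05 | Same, .001 | Between-arm test, .05 |
|---|---|---|---|---|
| 0.2 | 1.10 | 18% | 1% | 5% |
| 0.3 | 1.64 | 36% | 4% | 5% |
| 0.4 | 2.19 | 56% | 10% | 5% |
| 0.5 | 2.74 | 75% | 21% | 5% |

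By simulation at .05, a significant rise in the nasya arm with no significant group difference occurs in about 16%, 33%, 54% and 73% of trials respectively.

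**5. Direction.** With a drift of −0.2 to −0.5 SD, a significant rise in the nasya arm occurs in about 0.1% of trials or fewer. The problem therefore needs an upward drift, such as practice. Habituation, which lowers the response, would work against the hypothesis.

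**The case against.** **The between-group analysis is already planned.** This is true, and it limits the point. The fMRI analysis section states a between-group aim and the overview lists between-group tests. A reader might infer that the trial will ignore its control arm, or will declare success on a within-arm rise. The article says neither. What stands is that its hypothesis can be met in that way.

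**The trial is exploratory and only an article is shown.** Ranking contrasts is commonly left to the full protocol or the analysis plan, and a single deciding test is a confirmatory standard. A reader might infer that the article is at fault for naming no one deciding contrast; that demand goes too far here. The conflict between the printed hypothesis and the printed design is a different matter, because it is stated rather than omitted. The article also gives a directional hypothesis, a primary outcome and an a priori power claim.

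**The sentence on the control arm can be read either way.** This is accepted. The baseline measures in healthy individuals might be the controls' measures. The sentence needs aligning, but it does not independently repeat the within-arm hypothesis.

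**The illustration does not describe the planned inference.** This largely stands. It uses one scalar measure and an assumed drift. At the .001 voxel threshold the chances fall to about 1% to 21% per test point, and that is not a cluster-level calculation.

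**Conclusion.** The concern holds as a conflict within the article. The only stated hypothesis is a within-arm contrast, while the design and the fMRI analysis are between groups. As worded, the hypothesis can be met with no difference from the randomized control.

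The size depends on an unknown shared drift. If it is upward by 0.2 to 0.5 SD of change and nasya has no effect, a single-measure within-arm test is significant in about 18% to 75% of trials at .05, or about 1% to 21% at .001. The between-arm test stays at about 5% at .05. If the drift is downward, the problem does not arise in this form.

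A reader might also take the power figure as proof that a within-arm test was intended, since only the paired test at .05 exceeds 80% under standard formulas. The article does not support that, because its toolbox calculation cannot be reproduced from what is printed.

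**What to change.** 1. In Objectives, reword the hypothesis for the day-14 component: the change from day 1 (pre-procedure) to day 14 will be greater in the nasya group than in the control group. Align the control-arm sentence in Interventions with it.
2. Label within-group changes as supportive.
3. Keep the immediate response as a primary component, but state that it is an uncontrolled within-arm description that cannot by itself attribute an effect to nasya.
4. Apply the between-group contrast to each state for which controls have data. The Abstract gives participants task and resting scans, while Preparatory Phase mentions only resting-state mapping for controls. These statements must be reconciled first.
5. Restate Power Analysis for the between-group contrast. By the standard two-sample t formula it is about 63% at d=0.6, 30 per group and two-sided .05.

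**Cost.** The rewording itself needs no new data. Within-arm and immediate changes alone can no longer be reported as confirming the hypothesis, and the power statement needs rework. If controls turn out to have no task scans, the task part of the day-14 component would also be a within-arm description.
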